### Recruitment {15}

Patients will be recruited by telephone. We will contact participants in the MEDIDAS cohort study who meet the inclusion criteria for this study. The MEDIDAS cohort study is composed by elderly with different degrees of obstructive sleep apnea, recruited from a local basic health unit, after positive screening for sleep apnea symptoms.

## Assignment of interventions: allocation

### Sequence generation {16a}

Participants will be randomly assigned to either control or experimental group with a 1:1 allocation as per a computer-generated allocation list (https://www.randomizer.org/) using permuted blocks of four.

### Concealment mechanism {16b}

The bottles with hydroxychloroquine or placebo will be numbered in the handling pharmacy that will produce the capsules. Only the pharmacist will have access to the allocation list. Each participant will match the bottle with the number that the participant will receive in the plan. Both patients and researchers involved with either primary or secondary outcome measures will be blinded to the patient’s allocation.

### Implementation {16c}

Someone from outside the research team will generate the allocation sequence.

## Assignment of interventions: Blinding

### Who will be blinded {17a}

Trial participants, researchers involved in the study, outcome assessors will be blinded.

### Procedure for unblinding if needed {17b}

Unblinding will be permissible in case of severe adverse effects. The pharmacist with the allocation list will be contacted to inform the assigned group of the participant in question.

## Data collection and management

### Plans for assessment and collection of outcomes {18a}

#### Biochemical tests

Biochemical assessment will be performed on all participants at the beginning of the study and after 8 weeks of treatment. The exams will be held early in the morning, with participants fasting. Blood samples will be collected in five different sampling tubes with a capacity of 9 ml. The samples will be taken to the laboratory to measure plasma levels of ultra-sensitive C-reactive protein, total cholesterol, HDL-cholesterol, triglycerides, glucose, and glycated hemoglobin.

#### Peripheral arterial tonometry

The microvascular endothelial function will be determined by an automatic device (EndoPAT2000, Itamar Medical, Cesarea, Israel), with the technique already described. The cuff will be placed on the non-dominant arm, 2 cm above the cubital fossa, and RH-PAT tests on the pulp of each index finger will be performed. The basal pulse amplitude will be measured for 5 min. The arterial blood flow will be interrupted on one side for 5 min by insufflation of the cuff, with an occlusion pressure of 200 mmHg, or 60 mmHg above systolic blood pressure. After 5 min of occlusion, the cuff is deflated and reactive hyperemia, the RH-PAT sign, is registered in both hands for an additional 5 min. The contralateral finger is a control for changes in systemic vasodilation. The reactive hyperemia index (RHI) is automatically calculated by the RH-PAT equipment according to the manufacturer’s formula. RHI is defined as the ratio between post-deflation pulse amplitude, 90 to 150 s after the cuff is released, and the mean baseline pulse amplitude. This result is divided by the corresponding proportion of the control finger, and multiplied by a correction factor in relation to the baseline. Low RHI values are related to an inadequate endothelial vasodilator response.

#### Flow-mediated dilation of the brachial artery

High-resolution ultrasound equipment (Esaote) will be used to assess arterial endothelial function. A high frequency transducer will be used to obtain longitudinal images of the brachial artery walls. The images of diameter and arterial flow, at each moment of the protocol, will be recorded simultaneously on a computer with the aid of a capture card (Easycap). To minimize operational errors, both the transducer and the subject's arm will be positioned and maintained in the same position during the examination. Baseline images will be recorded for 1 min and then the pressure cuff on the forearm will be inflated to 200 mmHg and maintained for 5 min, characterizing reactive hyperemia. After deflating the cuff, 3 min of endothelium-dependent brachial artery dilation will be recorded. After the exam, the images recorded in MPEG will be converted to MP4 and then analyzed using specific software (Cardiovascular Suite) for the diameter and arterial flow before and after reactive hyperemia.

#### Portable sleep monitoring device

The portable sleep monitoring device Somnocheck Micro (Weinmann Medical Technology, Hamburg, Germany) will be attached to the patient’s wrist. The patient will also use a nasal cannula to register airflow. The device will be programmed to turn on at 22 pm and turn off at 10 am. A combination of photoplethysmography-derived pulse wave analysis and respiratory flow signals may enable differentiation between obstructive and central apnea and provide information regarding the extent of sleep fragmentation. In detail, respiratory effort derives by analyzing fluctuations of the pulse wave analysis signal caused by intrathoracic pressure changes during spontaneous breathing cycles. Central apneas, RERAs, mean and minimum oxygen saturation, and the apnea-hypopnea index will be reported according to the rules of the American Academy of Sleep Medicine. The portable sleep monitoring exam will be performed before and after 8 weeks of treatment.

### Plans to promote participant retention and complete follow-up {18b}

In order to promote participant retention and complete follow-up, all participants will be asked to provide, at the beginning of the study, their updated contact information.

### Data management {19}

The web-based application REDCap will be used for data entry and storage. Original study forms will be entered and kept on file at the participating site. Participant files will be maintained in storage for 2 years after completion of the study.

### Confidentiality {27}

All study-related information will be stored securely at the study site. All participant information will be stored in locked file cabinets in areas with limited access. All laboratory specimens, reports, data collection, process, and administrative forms will be identified by a coded ID [identification] number only to maintain participant confidentiality. All records that contain names or other personal identifiers, such as locator forms and informed consent forms, will be stored separately from study records identified by code number.

## Statistical methods

### Statistical methods for primary and secondary outcomes {20a}

Normally distributed data will be presented as mean and standard deviation. Data not normally distributed will be presented as median and interquartile range. The natural logarithmic transformation of the variable will be used to correct its non-normal distribution in analyses that assume the normal data distribution. The intervention arm (hydroxychloroquine) will be compared against the control for all primary analysis. We will use chi-squared test for binary outcomes, and *T* test for continuous outcomes. We will examine the residual to assess model assumptions and goodness-of-fit. The group × time interaction will be tested using generalized estimating equations. We will use the Bonferroni method to appropriately adjust the overall level of significance for multiple primary outcomes, and secondary outcomes. Results with a probability < 0.05 of alpha error will be considered statistically significant. Statistical analyses will be performed using SPSS software (SPSS Inc., Chicago, IL, USA).

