Evidence from studies in patients with rheumatic diseases converges to a role for HCQ in reducing cardiovascular risk. However, its cardiovascular effects in patients at higher cardiovascular risk but without rheumatic diseases are unknown.

Some common side effects of hydroxychloroquine, occurring in 1-10% of users, include anorexia, emotional lability, headache, blurred vision, abdominal pain, nausea, rash, and itching. Rarely, in 0.1–1% of high-dose users, Stevens-Johnson syndrome, cardiomyopathy, and retinopathy may occur.

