### Sample size {14}

Based on the effect size estimate of 0.3 standard deviations in the response of endothelial function after HCQ, for a 95% power and 0.05 level of alpha error probability, the sample size was estimated at 20 participants per group. Allowing for extra recruitment to compensate for losses, the sample size will be 25 participants per group, with a sum of 50 individuals.

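### The Bonferroni rule takes in the adverse-effect comparison without exempting harms, which makes a real excess harder to detect in a trial of 20 to 25 per group

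*Protocol article*

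**What the plan says.** Three statements in the protocol article combine.

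- Outcomes {12}, Secondary outcomes: the last of eight listed items is the comparison of the adverse-effect rate between the hydroxychloroquine and control groups.
- Statistical methods {20a}: "We will use chi-squared test for binary outcomes", with the significance rule "Results with a probability < 0.05 of alpha error will be considered statistically significant".
- The same section on multiplicity: "We will use the Bonferroni method to appropriately adjust the overall level of significance for multiple primary outcomes, and secondary outcomes". The number of tests is not given, and nothing sets harms apart from efficacy.

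On numbers, Sample size {14} says "the sample size was estimated at 20 participants per group" and, after an allowance for losses, "the sample size will be 25 participants per group, with a sum of 50 individuals". That calculation concerns endothelial function and not adverse effects. On event rates, the Hydroxychloroquine part of the background says: "Some common side effects of hydroxychloroquine, occurring in 1-10% of users, include anorexia, emotional lability, headache, blurred vision". No rate is given for any adverse effect, in either arm.

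**The concern.** Bonferroni guards against declaring a difference that is not there, which suits a list of efficacy outcomes where any one success could be claimed. For harms the costlier error is usually the opposite one, missing a true excess, and a stricter threshold makes that error more likely. In this trial the stricter threshold is applied to a comparison that is already weak at 20 to 25 per group. At stake is whether a moderate excess of common adverse effects would reach the only between-group criterion that the article states for harms.

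**Working it through.** **The plan's own figure.** The article gives no power for adverse effects, so there is none to reproduce. Its only calculation is for endothelial function: "Based on the effect size estimate of 0.3 standard deviations in the response of endothelial function after HCQ, for a 95% power". The two-sided formula gives 2 × (1.960 + 1.645)² / 0.3² ≈ 289 per group, not 20. That is a separate matter; only the group sizes are used here.

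**Inputs from the article.** 20 or 25 per group, 1:1 allocation, chi-squared test, nominal alpha 0.05 (taken as two-sided).

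**Assumed inputs.**
- *Endpoint:* the number of participants with at least one adverse effect.
- *Divisor:* 8 counts the secondary items as listed. 13 counts each variable: C-reactive protein, HbA1c, glucose, three lipids, apnea-hypopnea index, mean and minimum saturation, weight, systolic and diastolic pressure, adverse effects. 10 and 15 add the two primary measures. The thresholds are 0.05/8 = 0.00625, 0.05/10 = 0.005, 0.05/13 = 0.0038 and 0.05/15 = 0.0033.
- *Event rates:* as in the table below.

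**Method.** For each group size, list every 2×2 table and compute the uncorrected Pearson statistic, N(ad − bc)² divided by the product of the four margins. Then sum the binomial probabilities of the tables with p below the threshold.

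**Power, hydroxychloroquine rate v placebo rate:**

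| Rates | n per group | alpha 0.05 | 0.05/8 | 0.05/13 | 0.05/15 |
|---|---|---|---|---|---|
| 30% v 5% | 20 | 59% | 19% | 19% | 10% |
| 30% v 5% | 25 | 71% | 33% | 23% | 22% |
| 40% v 10% | 20 | 62% | 28% | 25% | 19% |
| 40% v 10% | 25 | 73% | 40% | 33% | 29% |
| 30% v 10% | 20 | 36% | 9% | 8% | 5% |
| 30% v 10% | 25 | 45% | 15% | 10% | 9% |
| 60% v 10% | 20 | 95% | 78% | 73% | 71% |
| 60% v 10% | 25 | 98% | 89% | 85% | 84% |

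The divisor of 10 falls between 8 and 13 throughout.

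**Events needed for significance.** With no placebo events, 4 hydroxychloroquine events suffice at alpha 0.05 for either group size. Under the correction 7 or 8 are needed, depending on divisor and group size.

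**Example 1: 8/20 v 2/20.** Chi-squared = 40 × (8×18 − 12×2)² / (20×20×10×30) = 4.8, p = 0.028. This is below 0.05 but above all four corrected thresholds. The Wilson limits are 0.219 to 0.613 and 0.028 to 0.301. The Newcombe interval for the difference of 0.30 runs from 0.30 − √(0.181² + 0.201²) = 0.03 to 0.30 + √(0.213² + 0.072²) = 0.53.

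**Example 2: 7/25 v 0/25.** Chi-squared = 50 × (7×25)² / (25×25×7×43) = 8.14, p = 0.0043. This passes at 0.05/8 and 0.05/10 but fails at 0.05/13 and 0.05/15. The Newcombe interval for the difference of 28 points is about 9 to 48 points.

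**The case against.** Five points can be made against this.

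- *A reader might infer that an excess of harm will be reported as no difference, or as evidence of safety.* The article does not say so. It defines statistical significance and draws no safety conclusion from its absence. This objection stands.
- *A reader might infer that the trial would miss an excess of any size, or that the correction alone is to blame.* Neither holds. The 60% v 10% case is found in most trials even at the strictest threshold. Without any correction, 30% v 10% has only 36-45% power. This stands too, and it is why removing the correction is not a complete remedy.
- *Harms are also handled patient by patient.* There are monitoring calls {11c}, discontinuation for severe effects {11b}, unblinding {17b} and serious-event reporting {22}. These are real safeguards, but none estimates the difference in adverse-effect rates between arms.
- *A condensed article may leave safety tables and intervals to a fuller document.* True, and their absence is not the point here. The point is a rule that the article does state.
- *This comparison is not presented as the safety basis of a later trial.* Correct. The Discussion in the abstract ties the multicentre trial to improvement in efficacy measures, the study is called exploratory, and recruitment will not resume.

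**Conclusion.** The concern holds in limited form. Read as written, the statistical section puts the adverse-effect comparison inside the Bonferroni family. For the assumed excesses of 25 to 30 points (30% v 5%, 40% v 10%), that lowers power from about 59-73% to about 10-40%. The figures rest on assumed event rates, a divisor of 8 to 15, a per-participant endpoint and the Pearson test without continuity correction. The final number recruited is not stated, so actual power may be lower. The direction of the effect depends on none of these, because any divisor above 1 makes a harm signal harder to reach. Severity is low: this is a cheap improvement in wording and does not show that harms would be misreported.

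**What to change.** In Statistical methods {20a}, limit the Bonferroni sentence to the efficacy outcomes. Add that adverse effects will be reported as counts and percentages per arm, with an unadjusted risk difference and a 95% confidence interval suited to small counts (for example Newcombe), and will not be judged by the corrected threshold. The interval shows how much excess remains compatible with the data, which matters because power stays limited even at alpha 0.05.

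The cost is a sentence or two and one interval per adverse-effect row, with no new data or participants. The change can still be made although recruitment has ended, since it concerns only how collected data are reported. The downside is that some chance imbalances in adverse effects will show intervals that exclude zero.

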#### Peripheral arterial tonometry

Peripheral arterial tonometry (PAT) is a non-invasive method of assessing endothelial function in clinical practice. The method was incorporated into several population and multicenter studies, such as the Framingham Heart Study. The results are based on digital pulse amplitude variation during reactive hyperemia induced by a 5-min forearm cuff occlusion. It is operator/interpreter independent and provides immediate results, which are advantages compared to FMD. The reactive hyperemia index (RHI) obtained by PAT is considered to correlate significantly with coronary endothelial function [20]. PAT is a predictor of cardiovascular risk in high-risk patients, according to several authors [21–24]. The method also has good reproducibility, according to studies by Brant et al and Reisner et al. [25] In two large population studies, totaling more than 10,000 participants, there is only a modest correlation between FMD and PAT [26, 27]. Therefore, both methods will be used in this study, in order to quantify aspects of both macro- and microvascular circulation and compare the two methods.

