### Outcomes {12}

#### Outcomes

##### Main outcome

Difference between the two groups on endothelial function measured by FMD (change of percentage of dilatation of brachial artery diameter from baseline) and PAT (change of reactive hyperemia index of finger from baseline) after 8 week of intervention.

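### Single-step Bonferroni for FMD, PAT and the secondary outcomes is valid, but Holm's step-down version would be a cheap, modest improvement for the second and later rejections

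*Protocol article*

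**What the plan says.** The section on statistical methods for primary and secondary outcomes {20a} fixes the multiplicity rule: "We will use the Bonferroni method to appropriately adjust the overall level of significance for multiple primary outcomes, and secondary outcomes". The overall threshold follows: "Results with a probability < 0.05 of alpha error will be considered statistically significant". Continuous outcomes are compared by t test.

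The main outcome has two measures: "Difference between the two groups on endothelial function measured by FMD (change of percentage of dilatation of brachial artery diameter from baseline) and PAT", the latter being the change in the reactive hyperemia index. The background section on peripheral arterial tonometry says that in two large population studies "there is only a modest correlation between FMD and PAT", and gives this as the reason for using both.

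The secondary outcomes list contains 12 continuous measures (C-reactive protein, HbA1c, glucose, total cholesterol, HDL, triglycerides, apnea-hypopnea index, mean and minimum saturation, weight, systolic and diastolic pressure) plus the adverse-effect rate.

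The sample size section {14} starts: "Based on the effect size estimate of 0.3 standard deviations in the response of endothelial function after HCQ, for a 95% power and 0.05 level". It arrives at 20 per group, raised to 25 for losses.

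**The concern.** Single-step Bonferroni holds both primary outcomes to 0.025 whatever the other one shows. Holm tests the smaller p value at 0.025 and, if that succeeds, the larger at 0.05. Both keep the family-wise error at 0.05 under any correlation, and everything Bonferroni rejects Holm also rejects. As a testing rule, then, the stated method is dominated.

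The trial is small and measures large-vessel and small-vessel function as separate objectives. If both respond, the second finding is the one that single-step Bonferroni is most likely to miss. The same applies, with a longer ladder of thresholds, to the secondary outcomes.

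**Working it through.** **Inputs from the document.** Two primary outcomes; overall level 0.05; t test on change; 20 evaluable per group; planning effect 0.3 SD.

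**Assumptions.** Two-sided tests, normal changes with SD 1, equal true effects unless stated, FMD–PAT correlation 0.2 (the document says only that it is modest).

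**The plan's own figure.** Read literally as a two-group comparison, n = 2(1.96 + 1.645)²/0.3² ≈ 289 per group, not 20. With 20 per group, power at 0.3 SD is 15% at 0.05 and 9% at 0.025. The figure 20 is met if 0.3 is read as Cohen's f for a group-by-time interaction with a pre–post correlation of 0.5, neither of which is stated. Noncentrality is then 0.3² × 40 × 2/0.5 = 14.4. Setting n·d²/2 = 10d² = 14.4 gives d = 1.2 SD of the change, with about 96% power at 0.05. The effects below therefore run from 0.3 to 1.2 SD.

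**Rejection rules for the primary pair.**
- Bonferroni shows both if both p values are below 0.025.
- Holm shows both if the smaller is below 0.025 and the larger below 0.05.
- At least one is shown, under either rule, if the smaller is below 0.025. This probability is the same by construction.

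**Closed form at correlation 0.** Let a be the power of one test at 0.025 and b its power at 0.05. Power for both is a² with Bonferroni and 2ab − a² with Holm. For example, at 1.0 SD: 0.793² = 0.63, and 2(0.793)(0.869) − 0.793² = 0.75.

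**Results with 20 per group.** The correlation 0.2 columns come from simulation, in runs of 40,000 to 100,000 trials. Entries are Bonferroni / Holm.

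| Effect on both (SD) | a | b | Both, corr. 0 | Both, corr. 0.2 | Per outcome, corr. 0.2 | At least one, corr. 0.2 |
|---|---|---|---|---|---|---|
| 0.3 | 9.4% | 15.2% | 0.9% / 2.0% | 1.4% / 2.9% | 9.4% / 10.1% | 17%, same |
| 0.8 | 58.1% | 69.3% | 34% / 47% | 37% / 49% | 58% / 64% | 80%, same |
| 1.0 | 79.3% | 86.9% | 63% / 75% | 64 to 65% / 76% | 79% / 85% | 94%, same |
| 1.2 | 92.3% | 95.9% | 85% / 92% | 86% / 92% | 92% / 95% | 99%, same |

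No simulated trial had a Bonferroni rejection that Holm missed. With 25 per group and 0.3 SD, power for both is 2.1% and 4.1%, and power per outcome 11.4% and 12.4%.

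**Only one outcome responds (1.0 SD and 0).** Power for the real one is 79 to 80% under either rule, with a difference of at most 0.2 points.

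**Error control.** With both outcomes null, the family-wise error is about 5% under both rules. With one outcome at 1.2 SD and the other null, the null one is rejected in about 2.4% of trials with Bonferroni and 4.7% with Holm, still within 5%.

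**Secondary outcomes.** For 12 continuous outcomes treated as one family (an assumption) with 20 per group, average power is about 55% with Bonferroni and 69 to 70% with Holm if all have a 1.0 SD effect. If six of 12 are real at that size, it is 55% and 59%. At 0.3 SD both are about 2.5%.

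**The case against.** The strongest reply is that nothing here is wrong. Bonferroni controls the error that the plan sets out to control, it is prespecified, and no section contradicts it or claims maximum power. The trial design section calls the study exploratory. All of that stands.

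A reader might infer that power is given away for nothing. The documents do not support that. Bonferroni yields 97.5% intervals for the two primary outcomes that agree with its tests, and Holm has no equally simple counterpart. Where estimates are meant to inform a later trial, this is a legitimate reason to prefer Bonferroni.

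A reader might also take the 11-to-12-point gain at 1.0 SD as the expected benefit. That effect is an assumption. At the literal 0.3 SD the gain is 1.5 points for both outcomes and under one point per outcome. Nor is joint significance a stated success criterion: the main outcome section lists FMD and PAT without requiring both.

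Finally, the Discussion reports that an interim analysis was done and mentions a significant finding, and the trial status section says that recruitment will not resume. Moving to a less strict rule after looking at data is not a free edit.

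These arguments reduce the point to a modest one. They do not remove it: Holm still controls the same error and never rejects less.

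**Conclusion.** The point holds as an optional improvement, not as the correction of an error. Holm would make a second primary finding, and later secondary findings, easier to establish at the same family-wise error. It does not change the chance of at least one significant primary outcome, and it does almost nothing if only one outcome responds.

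The size depends on the true effect: negligible in absolute terms at 0.3 SD, about 6 points per outcome and 11 to 13 points for both at 0.8 to 1.0 SD, and about 3 and 6 points at 1.2 SD. These figures rest on two-sided t tests, equal effects, 20 per group and correlation 0.2. At correlation 0 the joint gain is similar.

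It should not be inferred that Holm would repair the trial's power. The mismatch between 0.3 SD, 95% power and 20 per group, and the use of an unsplit 0.05 in the sample size, are separate matters that Holm leaves untouched.

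**What to change.** Optional. In the statistical methods section {20a}, name the Holm step-down form of Bonferroni instead of the single-step form. Apply it to the two primary outcomes and, as a separate family, to the efficacy secondary outcomes. Report Holm-adjusted p values beside unadjusted estimates and confidence intervals.

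The cost is a few words and no data or participants. The drawback is that an unadjusted interval may disagree with an adjusted p value about significance, so the report should say which one carries the inference.

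Timing matters because data have already been examined. Make the change only before unblinded analysis. Otherwise label Holm as post hoc and show it beside the prespecified Bonferroni result, or adopt it in the plan of the successor trial.
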